
#### ii) Cost-effectiveness outcomes

An economic evaluation will be conducted from the perspective of the society and the Health Service comparing the EIRA intervention vs. the usual care group at 12-months post-intervention.
*Outcome measure*
Incremental cost per quality-adjusted life years (QALYs) gained will be calculated. QALYs will be measured using the Spanish tariffs of the EuroQol-5D questionnaire [53]. The following costs will be taken into account: hospital care (emergency visits and stays), secondary care (visits to specialists), primary care (visits to physician and nurse), social care services (visits to social worker), outpatient diagnostic tests, medication use, group sessions attended, community resources used and loss of productivity (days off work). This information will refer to the last 12 months prior to study entry and to the subsequent 12 months. Use of healthcare resources and lost productivity will be assessed through the patients’ clinical history and also the Client Service Receipt Inventory [65]. Information on the use of medicines (active substance, dose, and units supplied) will also be collected. The unit costs of public healthcare services will be obtained from the Official Bulletin of the Government. Costs of privately funded services will be obtained from published tariffs. The mean price per milligram of active substance will be calculated using the prices of the generic versions of all the presentations as reported in the Spanish Vademecum. Productivity losses will be calculated based using information on the minimum and average daily wage in Spain [66].

#### iii) Implementation outcomes

Early appropriateness and acceptability. It will be evaluated in professionals and participants by means of a survey prior to the start of the intervention.Final appropriateness and acceptability. It will be evaluated in professionals and participants by means of a survey. What is more, discussion groups will be held at the end of the intervention with the professionals and participants.Adoption. The proportion of professionals who express their willingness to participate in the study between of total of potential professionals prior to the start of the intervention.Feasibility. On the basis of the calculation of participation, recruitment and retention rate at 12 months post-intervention.Fidelity of the motivational interview model. The quality of the motivational interview delivered will be assessed by coding video recordings of an acting patient session with the “motivational interviewing assessment scale” [67] before and after the training course provided.Fidelity of the planned intervention. The degree of compliance of the activities recorded in the case report form (CRF) will be analysed.Fidelity of the implementation. The degree of compliance of the implementation strategies.Cost of time invested in training and organisational meetings to carry out the intervention.Penetration. The proportion of professionals who have integrated the intervention into their usual clinical practice after completing theintervention.

### Sample size

The sample size was calculated on the basis of data from the literature and some results of phase II. We expect a difference in the percentage of people who show a positive change in one or more of the three behaviours between the two groups of at least 8%. Assuming 30% patient loss to follow-up, alpha risk of 5%, beta risk of 20%, and an intracluster correlation of 0.01 [68], we consider that it is necessary to study a minimum of 140 participants for each PHC centre, a total of 3640 people (1820 for each of the two groups, 13 PHC centre per group). PASS software was used to compute the sample size [PASS 14 Power Analysis and Sample Size Software (2016). NCSS, LLC. Kaysville, Utah, USA, ncss.com/software/pass]. Sampling was done in order to fulfil an established sex and age quota which is proportional to the last general population census.

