### Study objectives and hypotheses

This hybrid trial has the following primary objectives:To evaluate the effectiveness and cost-effectiveness of a complex multiple risk intervention on reducing tobacco use, enhancing adherence to Mediterranean dietary pattern and increasing physical activitylevel in 12 months to baseline compared with usual care.To assess the effectiveness of an implementation strategy in terms of acceptability, adoption, appropriateness, feasibility, fidelity, implementation cost and penetration.

Furthermore, other secondary objectives related to the effectiveness of the intervention will also be evaluated: its impact on reducing cardiovascular and depression risksas well as depressive and anxiety symptoms and incidence of major depression.

We hypothesise that the proportion of people who show a positive behaviour change with regard to any baseline behaviours will be higher among people who receive the intervention than people who receive usual care. We also hypothesise that the intervention will reduce cardiovascular risk, incidence of major depression, depression risk and depressive and anxiety symptoms.

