### Intervention

The intervention is based on the Transtheoretical Model (TTM) [32, 33] and will be made by physicians and nurses in the routine care of PHC practices according to the conceptual framework of the “5A’s”: Assess, Advise, Agree, Assist, and Arrange-follow up [34]. It will consist of a first visit of screening in which PHC professional will assess person level of behaviour and stage of change (“Assess”). Behaviours will be assessed by one question to know tobacco use during the last month, two validate questions about the daily consumption of fruits and vegetables [35] and the Brief Physical Activity Assessment Tool [36, 37]. Stages of change will be assessed on the basis of core constructs of the TTM for each of the target behaviours (see Table 1) [32]. Subsequently, the PHC professional will advise the person (“Advise”), will agree with him/her on a realistic set of goals (“Agree”), will assist to anticipate barriers and will develop a specific action plan (“Assist”), and will arrange follow-up support (“Arrange”).

**Table 1 Tab1:** Core constructs of the Transtheoretical Model (Prochaska et al. 2008) [32]

Stages of Change	Description
Precontemplation	No intention to take action within the next 6 months
Contemplation	Intends to take action within the next 6 months
Preparation	Intends to take action within the next 30 days and has taken some behavioural steps in this direction
Action	Changed overt behaviour for less than 6 months
Maintenance	Changed overt behaviour for more than 6 months
Termination	No temptation to relapse and 100% confidence

Intervention is based on the results of previous phases (preclinical, phase I and phase II) [23–25, 38–42]. It will have a maximum duration of 12 months and it will be carried out to three different levels (individual, group and community) according to stages of change and unhealthy behaviour (see Table 2). It will focus on all three target behaviours and PHC professional together with the participant will develop priority actions on one or more of these behaviours.

**Table 2 Tab2:** Description of intervention

	Unhealthy behaviours								
	Tobacco use			Insufficient physical activity			Non-adherence to Mediterranean dietary pattern		
Level of intervention	Individual	Group	Community	Individual	Group	Community	Individual	Group	Community
Stages of change									
Precontemplation	Very brief intervention + SMS			Very brief intervention + SMS			Very brief intervention + SMS		

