#### i) Effectiveness outcomes

The effectiveness of the complex multiple risk behaviour intervention in comparison with the usual care at maximum 12 months post-intervention will be measured by:
*Primary outcome measures*
Positive change in baseline eating behaviour: adherence to the Mediterranean dietary pattern in low adherence people. For the evaluation, the 14-item Questionnaire of Mediterranean diet adherence (PREDIMED study) will be used [49]. The positive change has been defined as obtaining eight or fewer points at the study entry and nine or more at the end of the study in this questionnaire.Positive change in baseline physical activity behaviour: sufficient physical activity level in insufficiently active people. For the evaluation, the International Physical Activity Questionnaire will be used [50]. The positive change has been defined as having a low physical activity level at the study entry and a moderate or high physical activity levelat the end of the study.Positive change in baseline smoking behaviour: self-reported continuous abstinence [51]. For the evaluation, the interview will be used and optionally the cooximetry. The positive change has been defined as smoking at the study entry and not smoking at the end of the study. We will measure the punctual and continuous abstinence at these two times.

*Secondary outcome measures*

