### Analysis

#### Effectiveness of intervention

All analyses will be carried out in accordance with the intention-to-treat principle. Depending on the characteristics of the variables, it will be assessed if it is appropriate to make multiple imputationin the variables with missing data or to make a conservative approach to data loss. Multiple imputation will be the preferred technique for dealing with missing data, and the conservative approach will be used when the data indicate that it is the most appropriate. Multiple imputation by chaining equations procedure will be used to obtain at least 20 imputed datasets and Rubin’s rules will be used to combine them [72]. Sensitivity analyses will be performed for the primary and secondary outcomes to assess the impact of the multiple imputation or the conservative approach to data loss.

Descriptive and bivariate analyses will be calculated for all variables of interest. We will use cluster specific methods because PHC centres will be randomised. In order to analyse the effect of the intervention on each outcome measure, we will use hierarchical linear or logistic regressions models for clustered data. We will also analyse the variables associated with the change in the adherence to the Mediterranean diet, physical activity level and smoking cessation adjusting for possible confounding variables. Final models will be chosen coherently with the study objectives and the nature of the variables (potential confounders, significant and clinically relevant variables). The interactions and collinearity of the models will be evaluated. The size of the effect (Cohen’s d) will also be calculatedand the number needed to treat will also be calculated..

The level of significance of the models will be set at 5%. Stata/SE v.15 or higher (StataCorp, LP, TX) and R version 3.4.4 or higher will be used for statistical analysis.

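### The trial is hypothesised and sized on one any-of-three composite that is not among its listed outcomes, so the stated 80% power belongs to none of the three listed primary outcomes and the deciding result is not fixed

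*Protocol article*

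**What the plan says.** All references are to the protocol article.

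- **Study objectives and hypotheses.** The behaviour hypothesis reads: "the proportion of people who show a positive behaviour change with regard to any baseline behaviours will be higher among people who receive the intervention", usual care being the comparator. This is one composite.
- **Sample size.** The calculation uses the same composite, worded as "percentage of people who show a positive change in one or more of the three behaviours between the two groups of at least 8" per cent, with alpha 5%, beta 20%, intracluster correlation 0.01 and 30% loss. It gives 140 people per centre, 13 centres per group and 3640 people in all.
- **Effectiveness outcomes, primary outcome measures.** Three endpoints are listed: "adherence to the Mediterranean dietary pattern in low adherence people"; "sufficient physical activity level in insufficiently active people"; and abstinence in people smoking at entry. Each has its own baseline condition. The composite is in neither the primary nor the secondary list.
- **Analysis, Effectiveness of intervention.** A hierarchical model is fitted for each outcome measure, and "The level of significance of the models will be set at 5" per cent.
- **Analysis, Effectiveness of implementation strategy.** The composite returns here as the dependent variable of the models that relate implementation to effectiveness. It is not named as the endpoint of the randomised comparison.

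**The concern.** Three things a protocol itself must fix are all stated here, and they do not match: the hypothesis, the endpoint behind the sample size, and the primary outcome. A reader of the results could take the composite as the deciding test, because it is what was hypothesised and powered. The reader could equally take the three listed behaviours, because they carry the primary label.

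Mixed results would expose the gap. If the composite were null and physical activity positive, the article would support either a negative or a positive verdict. The allocation is open and the behaviours are largely self-reported, so a choice of headline result made after the data are seen would be hard to defend. The stated 80% power would also be quoted beside outcomes for which it was never calculated.

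**Working it through.** **Inputs from the document.** 13 centres per arm, 140 recruited per centre, 30% loss, intracluster correlation 0.01, alpha 5%, power 80%, difference 8%.

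**Assumptions.** The test is two-sided, and 8% means 8 percentage points. The control-group rate is not given, so a range is used.

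**1. The plan's own figure, for the composite**

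- Evaluable per centre: 140 × 0.70 = 98.
- Design effect: 1 + (98 − 1) × 0.01 = 1.97.
- Effective size per arm: 13 × 98 / 1.97 = 647.
- Power for two proportions, p and p + 0.08, n = 647 per arm:

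| Assumed control rate | Power (normal) | Power (t, 24 df) |
|---|---|---|
| 25% | 0.89 | 0.86 |
| 30% | 0.86 | 0.83 |
| 40% | 0.83 | 0.79 |
| 46% | 0.82 | 0.79 |
| 50% | 0.82 | 0.79 |

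- In reverse, at a 46% control rate with continuity correction, 637 effective per arm are needed. That is 95.1 evaluable per centre, or 95.1 / 0.70 = 136 recruited, and 26 × 136 = 3536. This is within 3% of 3640.

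So 3640 is a sensible number for the composite. Exact reproduction is not possible without the control rate.

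**2. What the calculation says about a listed outcome**

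Nothing. A listed outcome has a different denominator and its own control rate and difference, and the article gives none of these. Three invented scenarios show how far the answer can move:

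- *Gain shared by two behaviours.* Two equal, independent behaviours produce the 8 points, with 67–80% of participants at risk for each. At a composite control rate of 42%, each behaviour's control rate is 1 − √0.58 = 0.238 and its intervention rate 1 − √0.50 = 0.293, a gain of 5.4 points. With 67% at risk there are 65.3 per centre, design effect 1.643 and effective size 13 × 65.3 / 1.643 = 517 per arm, so power is 0.51. Over composite control rates of 25–46% the range is 0.51–0.60.
- *Gain from one behaviour only.* Same set-up at 42%, with 80% at risk and only that behaviour improving. The needed gain is 0.08 / (0.80 × (1 − 0.238)) = 13.1 points, on an effective size of about 575 per arm, and power exceeds 0.99.
- *Small subset, low control rate.* With 30% at risk, a 10% control rate and 8 points, there are 29.4 per centre and an effective size of 298 per arm. Power is 0.80.

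Component power therefore runs from about half to near certainty, depending on figures the article does not give.

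**3. Error rate if any one of three 5% tests counts as success**

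- Independent tests: 1 − 0.95³ = 0.143.
- Simulated correlated tests: 0.125 at correlation 0.5 and 0.099 at 0.8.
- If the composite alone decides: 0.05.

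**4. Cost of three confirmatory tests at 0.05/3**

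- For an 8-point difference, with every participant counted for each outcome, power at 3640 is 0.69–0.78 (control rates 46% down to 25%).
- Restoring 80% would need about 152–240 per centre, or 26 × 152 = 3952 to 26 × 240 = 6240 people.

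**The case against.** The best defence is that the article does identify its deciding test. It has one behaviour hypothesis, it is sized for that hypothesis, and the implementation section treats change in any of the three behaviours as the meaning of effectiveness. The three listed outcomes can then be read as the parts of the composite, and alpha is 5%. This reading is reasonable and is the one the fix adopts. But the article does not state it: the primary list contains only the parts, and the analysis section models each outcome measure.

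A second defence is that multiplicity rules belong in the statistical analysis plan, which is not shown. That stands for the adjustment method. It does not remove the mismatch, because such a plan could settle it only by departing from the primary outcome list or from the hypothesis and sample size.

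Stronger readings are tempting and are not supported:

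- *The false-positive rate is 14.3%.* That needs independent tests and a rule that any one success suffices. No section states such a rule, and the outcomes come from overlapping people in the same centres.
- *Each behaviour is underpowered.* This depends on how the 8 points divide between behaviours; the second and third scenarios above reach 80% or more.
- *The composite is diluted.* People enter on brief screening tools, among them "two validate questions about the daily consumption of fruits and vegetables", while success is scored on longer instruments, so someone may screen in yet be unable to improve on one of them. If 10% were at risk on none, 8 points would become 8 × 0.90 = 7.2, with power about 74% at control rates of 40–50% and 82% at 25%. The 10% has no source, and eligibility already requires two unhealthy behaviours.

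**Conclusion.** The concern holds as an inconsistency within the document. The hypothesis and the sample size use one composite; the primary outcome list uses three other endpoints; and the composite is in neither outcome list. The stated 80% power therefore applies to none of the listed primary outcomes, and the article does not fix which result decides the trial.

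The sample size is not shown to be wrong. For the composite, 3640 people give about 82–89% power by the normal approximation, or 79–86% with 24 degrees of freedom, assuming a two-sided test and control rates of 25–50%. An inflated error rate is conditional: it arises only if success on any one of three outcomes is accepted, and is then roughly 10–14% depending on correlation. The component-power and dilution figures are illustrations, not findings.

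**What to change.** In the primary outcome measures, name the composite as the single primary outcome: positive change in at least one of the three behaviours from baseline to 12 months, among all participants of the randomised centres under intention to treat, tested at 5%. State that a participant who is not at risk on an instrument at baseline counts as unchanged on that behaviour. Report diet, physical activity and smoking as components, each with a confidence interval. An analysis limited to people at risk on at least one baseline outcome instrument can be a sensitivity analysis. It should not replace the intention-to-treat comparison, because it drops enrolled participants.

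If the three behaviours are to remain co-primary, specify a multiplicity procedure such as Holm, and state in the Sample size section that the 80% power refers to the composite only.

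The first option is a change of wording in the protocol and analysis plan, with no new data and no change to the 3640 or to alpha. Its price is that the three behaviours lose stand-alone confirmatory status. The second keeps that status but costs power on each behaviour, or a larger trial.

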### Recruitment

Several interactive and passive recruitment strategies will be considered to increase the feasibility of achieving the target sample size [69]. Participants will be recruited for hybrid trial at PHC centres through five methods: 1) at the time of visit as part of usual care; 2) self-administered questionnaires delivered in the waiting room or in the admission desk; 3) a part-time training recruiter; 4) advertising by posters in the PHC centres and 5) phone calls to selected patients from review of electronic health records. Method of recruitment should be registered for each participant enrolled. Recruitment will carry out during six months. The facilitator and the leader of the study (see Table 3) will have a crucial role to monitor recruitment. PHC professionals and participants will not receive any financial incentives for enrolment; however, there will be the possibility to set managerial goals related to recruitment.

### Assignment of intervention

The allocation schedule for random assignment of intervention to PHC centres will be computer generated at a central location (IDIAP Jordi Gol, Barcelona, Spain). For each of the seven Spanish Autonomous Communities, we will randomly allocate half of the PHC centres to the intervention group and the other half to the control group. In total, 13 PHC centres will be allocated to the intervention group and 13 other to the control group. The allocation will not be concealed at PHC centres and no blinding will be done.

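### Centres are randomised within seven Autonomous Communities, but the analysis section does not secure community as a term in the arm comparison; if it is omitted and communities differ appreciably, precision is forgone.

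*Protocol article*

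**What the plan says.** Under Assignment of intervention, the Protocol article allocates centres separately within each region: "For each of the seven Spanish Autonomous Communities, we will randomly allocate half of the PHC centres to the intervention group". The overall split is equal: "In total, 13 PHC centres will be allocated to the intervention group and 13 other to the control group". Autonomous Community is therefore a stratification factor with seven levels.

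Under Analysis, Effectiveness of intervention, the reason given for allowing for clustering is the centre alone: "We will use cluster specific methods because PHC centres will be randomised". The model is given as a class: "we will use hierarchical linear or logistic regressions models for clustered data". The terms are left to a selection rule: "Final models will be chosen coherently with the study objectives and the nature of the variables (potential confounders, significant and clinically relevant variables". Community is neither named nor excluded.

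The Sample size section uses a difference of 8 percentage points in the proportion with a positive change in at least one behaviour, 30% loss, 80% power and "an intracluster correlation of 0.01". It takes no credit for stratification.

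**The concern.** Balancing centres within communities largely removes differences between communities from the comparison of arms. The estimate is then more precise than in an unstratified trial. The analysis shows that gain only if the model knows about the strata. Without a community term, variation between communities is counted as ordinary variation between centres and stays in the standard error.

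The selection rule is a poor way to bring the factor in. A factor balanced by design will tend not to look like a confounder, and a significance test on seven levels with 26 centres is weak and depends on the data. The factor by which the trial was randomised would then enter by later judgement, in a trial without blinding. At stake are intervals wider than the design warrants and a lower chance of detecting a real effect.

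**Working it through.** **Inputs from the Protocol article.** 26 centres, 13 per arm; 140 per centre with 30% loss, so m = 140 × 0.7 = 98 analysed; difference 0.08; ICC ρ = 0.01; alpha 5%; power 80%.

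**Assumptions, not in the document.** Control rate 42% (so 50% under intervention, mean p = 0.46); six communities with four centres and one with two; a two-sided test; analysis of centre proportions as an approximation to the hierarchical model. The community share s of the between-centre variance is unknown and is varied.

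**Plan's own figure.** 26 × 140 = 3640 is exact. The design effect is 1 + (98 − 1) × 0.01 = 1.97. The control rate is not given, so the 1820 per group can only be approximated. With a control rate of 40-50% and a continuity correction the result is 1768-1793 per group, within 3%; without the correction it is at most 1726.

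**True standard error under stratified allocation.** Only the within-community part of the centre variance remains:

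SE_true = √{ p(1−p) × [(1−s)ρ + (1−ρ)/m] × 2/13 }

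Here p(1−p) = 0.46 × 0.54 = 0.2484 and (1−ρ)/m = 0.99/98 = 0.010102.

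**Standard error reported without community.** Each arm has 13 centres, in communities contributing 2,2,2,2,2,2,1. The community part of the variance enters the within-arm variance with factor (13 − 25/13)/12 = 0.923:

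SE_model = √{ p(1−p) × [(1−s)ρ + 0.923sρ + (1−ρ)/m] × 2/13 }

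For s = 50%:
- SE_true = √(0.2484 × 0.015102 × 2/13) = 0.0240
- SE_model = √(0.2484 × 0.019717 × 2/13) = 0.0275
- Ratio 1.14

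**Results.** The standard-error excess comes from these formulas. Type I error and power come from 40,000 simulations per scenario, with 24 degrees of freedom without community (26 − 2) and 18 with it (26 − 7 − 1).

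| Share s | SE too wide by | Type I error without | Power without | Power with | Difference |
|---|---|---|---|---|---|
| 0% | 0% | 0.050 | 79.2% | 78.1% | −1.1 |
| 10% | 2% | 0.045 | 79.2% | 79.6% | +0.4 |
| 25% | 6% | 0.038 | 80.8% | 83.2% | +2.4 |
| 50% | 14% | 0.029 | 82.6% | 88.3% | +5.7 |
| 75% | 24% | 0.019 | 84.5% | 93.1% | +8.6 |

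With the term, simulated type I error was 0.050 to 0.052.

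**Break-even.** The term raises the critical value from 2.064 (24 df) to 2.101 (18 df), a ratio of 0.982. It pays once SE_model/SE_true exceeds 1/0.982 = 1.018, which happens at s of about 7.6%.

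**Sensitivity.**
- Control rate: p(1−p) cancels from the SE ratio. At a 30% control rate, power without and with the term is 84.7% and 86.6% (s = 25%), 86.5% and 91.3% (50%), 88.4% and 95.3% (75%).
- ICC: at 0.05 and s = 50%, power is about 35% without and 55% with the term. The low level itself comes from an ICC five times the planned one, not from the omission.
- Fewer analysed per centre: with 25 (an assumption, for example smokers only), 0.99/25 = 0.0396. At s = 50% the ratio is √[(0.0496 − 0.005 × 0.077)/(0.0496 − 0.005)] = 1.05, an excess of about 5%.

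**The case against.** The strongest reply is that the article states a class of model, not a list of terms. A hierarchy can hold centres within communities, and a condensed article commonly leaves the list to an analysis plan, which is not shown here. This stands to the extent that one cannot say the planned model excludes community, though a reader might infer it. But the section is not simply silent: it gives a rule for choosing terms, and that rule does not secure the stratum. The rule may govern only the exploratory models of who changes behaviour, since it follows directly on them. In that case the arm comparison has no stated rule for the stratum, and the same sentence is needed.

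Other stronger readings also fail:

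- **Power is lost whenever communities differ.** Below a share of about 7-8% the six degrees of freedom cost more than the term returns.
- **The trial is underpowered or its test invalid in the harmful direction.** At ICC 0.01 power without the term is about 79% to 85%, and type I error falls below 5%. The loss is relative to an analysis that uses the strata.
- **Community cannot be a confounder.** Allocation balances centres, not participants. The 140 per centre is a minimum, losses may differ, and each behaviour outcome concerns only people with that behaviour at baseline.
- **The same loss applies to each of the three behaviours.** Only the any-of-three comparison was simulated, and the excess shrinks when fewer people per centre contribute.

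The documents give no community share of variance. Local research teams, regional coordination and local adaptation make some difference plausible but do not measure it.

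**Conclusion.** The point holds as a gap in how the analysis is fixed: randomisation is stratified by Autonomous Community, and the stated rule does not ensure that the arm comparison reflects it. If community is omitted, the arm-effect standard error is overstated. For the any-of-three comparison the excess is minor at a community share of 25% or less and material at 50-75%. The error is conservative. These sizes rest on the assumed control rate, centre layout and community share, and on the centre-level approximation. The direction does not depend on the particular control rate. The change is worth making because the gain can reach several points of power and the worst-case cost is about one.

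**What to change.** Add to Analysis, Effectiveness of intervention, that Autonomous Community, as the stratification factor of the randomisation, is included in every arm comparison regardless of its significance, for example as a fixed factor. State that the arm effect is tested against a small-sample reference distribution, about 18 degrees of freedom for a fixed factor with 26 centres, because large-sample tests become too liberal with six more centre-level terms. A random community level would also fit the stated model class; whichever is chosen should be fixed in advance. Say that the existing rule for choosing terms applies only to additional covariates.

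The cost is two or three sentences and, with the fixed factor, six degrees of freedom: about 1 point of power (79.2% to 78.1% under the assumptions above) if communities do not differ. The sample size need not change.
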